#### Secondary outcomes

Secondary outcomes will include the level of momentary, positive and negative self-esteem, resilience, emotional well-being, positive and negative schematic beliefs of self, psychological distress, functioning, subjective quality of life, general psychopathology, clinical symptoms and health-related quality of life, service use (including admission to inpatient services) and cost, which will be compared between the experimental and control condition at post-intervention and at 6-month follow-up (H2). In addition, all secondary outcomes (incl. levels of global self-esteem, operationalized using the total score of the RSES (see previous section)) will be compared between the experimental and control condition and at 18- and 24-month follow-up (H3).

Momentary self-esteem will be assessed with four items, rated on a 7-point scale, using the ESM [78, 79]. The mean score will be used for analysis. Positive and negative self-esteem will be measured with the SERS, which is a 20-item rating scale to assess these two dimensions of self-esteem separately with good reliability and validity [80]. The total sum score of the positive dimension and the total sum score of the negative dimension will be used in the analysis. Momentary resilience will be assessed with the ESM positive affective recovery from event-related stress in daily life (operationalized as the return to baseline levels of positive affect following event-related stress) [31, 74, 76, 81]. We will assess emotional well-being using the Positive and Negative Affect Scale (PANAS) [82] based on the total sum score of the negative affect items and the total sum score of the positive affect items. Also, a 5-item ESM measure will be used for assessing negative affect and a 4-item ESM measure of positive affect [31, 74, 83]. For both measures, a mean score will be used in the analysis. The Brief Core Schema Scale (BCSS) will be used as an established measure of positive and negative schematic beliefs of self and others [84]. The following four total scores (all consisting of six items) will be obtained for use in the analysis: negative-self, positive-self, negative-others, and positive-others. Psychological distress will be measured with the Kessler Psychological Distress Scale (K10), which is widely used and well-validated in youth [85, 86]. A total sum score ranging from 10 to 50 will be used for analysis.

The Social and Occupational Functioning Assessment Scale (SOFAS) [87] and the Global Assessment of Functioning (GAF) scale [88] will be used as a well-validated measure of functioning in youth [86]. The overall level of functioning rated by researchers on a scale of 0 to 100 will be used in the analysis.

Subjective quality of life will be measured with the World Health Organization Quality of Life Instrument-Brief (WHOQOL-BREF) [86, 89]. Mean scores of all four domains (physical health, psychological, social relationships, environment) will be used. The revised Symptom Checklist (SCL-90-R) will be used as a reliable and valid measure to assess general psychopathology in youth [86, 90]. The measure consists of 90 items, which will be rated on a 5-point scale. The total sum score of the SCL-90-R will be used for analysis. We will use the 24-item version of the Brief Psychiatric Rating Scale (BPRS) [91, 92] as a validated interviewer measure to assess clinical symptoms of psychopathology in youth [86]. All items are rated on a 7-point scale and, for the analysis, the BPRS total score will be computed.

The Trimbos Institute and Institute of Medical Technology Assessment Questionnaire for Costs associated with Psychiatric Illness (TiC-P) [93] will be used to collect data on service use (including admission to inpatient services) and cost for cost-effectiveness analysis. Last, data on health-related quality of life will be operationalized by quality-adjusted life years (QALYs), which will be calculated based on the EQ-5D 5-level version of the “EuroQoL” group (EQ-5D-5L) for cost-utility analysis [94].

#### Process evaluation

A process evaluation will be performed following the methodology of realist evaluation [95]. Initial program theories will be developed based on transcribed data from a focus group with stakeholders as well as expert interviews. Overarching program theory and accompanying context-mechanism-outcome configurations will be tested among intervention users (individual interviews with participants who have completed the SELFIE intervention) as well as those who deliver the intervention (focus group with SELFIE therapists), through iterative data collection. Atlas.Ti will be used as software to support the process of our analyses.

#### Acceptability, adherence, and fidelity

We will carefully assess acceptability, safety, adherence, and fidelity of the SELFIE intervention. Participants in the experimental condition will be asked to complete a debriefing questionnaire, which assesses acceptability, satisfaction, and whether or not there were beneficial effects of the EMI tasks and sessions. Also the Working Alliance Inventory (WAI) [96] will be completed by the participant and the SELFIE therapist providing the SELFIE intervention. Adherence to the intervention will be assessed using the implicit EMI adherence data recorded by the app (e.g., number and duration of completed EMI interactive, enhancing and consolidating tasks). Further, the attended face-to-face sessions will be audio recorded and adherence will be rated on a visual analog scale (ranging from 0 = “not at all” to 11 = “very much”) by a clinical psychologist or researchers (supervised by a clinical psychologist).

#### Other measures

A socio-demographic schedule will be used to assess basic socio-demographic and clinical characteristics including age, gender, employment status, and level of education. Resilience will be assessed with the Temperament and Characteristics Inventory (TCI) [97]. Last, other confounders, such as alcohol and substance use (Composite International Diagnostic Interview (CIDI), sections B, J, and L) [98], medication use, treatment classification, and social support (Childhood Experience of Care and Abuse (CECA), section social support) [67], will also be assessed.

### Sample size

Previous studies demonstrated that third-wave cognitive behavioral therapy (CBT) [22, 99, 100], including CBT focusing on self-esteem [51, 101], may lead to reductions in symptoms of psychopathology of moderate to large effect size. In line with previous research, the power calculation is based on the primary outcome of level of self-esteem as measured with the RSES [51]. Power simulation in the R environment indicated that a sample size of 130 participants (65 per condition) is sufficient to test our primary hypothesis of the effect of condition (SELFIE + TAU vs. TAU) on self-esteem, while controlling for self-esteem at baseline. Specifically, this will allow us to detect an effect size (standardized mean difference (SMD)) of 0.3 (experimental vs. control condition), i.e., a difference that is considered clinically relevant, at (at least) post-intervention or 6-month follow-up with a power of 0.87 (primary hypothesis), and, at long term, (at least) at one of the post-intervention and follow-up time points (6-month, 18-month, and 24-month follow-up), with a power of 0.82 when testing at alpha = 0.05 using linear mixed modeling. Based on our previous and ongoing work, we will allow for a 25% attrition rate at 2-year follow-up, which will result in a loss to follow-up of around 22 individuals per condition on average (see Fig. 1). Hence, we will recruit a total sample of 174 participants (87 experimental, 87 control condition) at baseline.

### Randomization and blinding

Each participant will be randomized at a 50:50 ratio to the experimental or control condition after completing the baseline assessment. Randomization will be conducted through a computer-generated sequence, stratified by region of a collaborating center or as external admission. The assessors will be blind to the allocation of subjects when assessing participants at post-intervention, 6-month, 18-month, and 24-month follow-up. After random allocation to the experimental condition, the names and contact details of the participants will be passed on to the SELFIE-therapist providing the SELFIE intervention. This will be done through an independent researcher. This researcher will inform the assessors when assessments at post-intervention and follow-up need to take place for each individual participant. The design of this study is single blinded, because SELFIE therapists and patients cannot be masked towards the allocation of patients to the experimental or control condition. Any data specific to the intervention condition (e.g., on treatment fidelity) will be stored in a separate database. Any breaks in masking will be documented in the trial master file and another assessor will be allocated to complete the next set of assessments where possible.

### Assessment of safety

Serious adverse events (SAE), which include any serious incidents that result in death, persistent or significant disability or incapacity, require (extension of) hospitalization or are life threatening, will be monitored and collected throughout the study period. In case of occurrence, SAEs will be reported to the accredited Medical Ethics Review Committee (MERC), the Data Monitoring and Ethics Committee (DMEC), and the Trial Steering Committee (TSC). While carefully documented, it is not expected that any SAE will occur as a result of the intervention. The DMEC will advise on any ethical or safety concerns, monitor evidence for intervention harm (e.g., SAEs) for the experimental condition, and review whether these events are in line with expectations. If deemed necessary, the DMEC can recommend to the Coordinator and TSC for interim analyses to be conducted and the trial to be terminated prematurely. All reported (serious) adverse events will be reported in publications of findings from this study.

### Statistical analysis

A full statistical analysis plan will be written and published prior to unblinding of the study and before any analysis is being undertaken. The trial data set will be accessed by the investigators to test the primary hypothesis of an improvement in self-esteem at post-intervention and 6-month follow-up in a priori planned statistical analysis when data collection for assessments at 6-month follow-up has been completed while retaining masking of assessors until the last assessment of the last participant at 24-month follow-up. We will use a linear regression model with the primary outcome of self-esteem at post-intervention and 6-month follow-up entered as the dependent variable and self-esteem measured at baseline, condition (SELFIE + TAU vs. TAU), time (as a two-level factor), center (as a four-level factor), the baseline × time interaction, and a time × condition interaction term as independent variables, in line with the intention-to-treat principle. All randomized participants will be included in the analysis and will be analyzed according to the intention to treat principle. Residuals within subjects will be allowed to be correlated with a completely unstructured variance-covariance matrix to take within-subject clustering of repeated measures into account. We will fit the model using Restricted Maximum Likelihood (REML [102]) in Stata 15 [103], which allows for all available data to be used assuming that data is missing at random if all variables associated with missing values are included in the model [104, 105]. Therefore, potential bias due to attrition over the study period, differences between centers, or as a function of baseline self-esteem will be minimized by the model. We will make every effort to assess all participants at post-intervention and follow-up. To test the main effect of condition, an omnibus test of no difference between the two conditions at all two time points (Wald-type test with df = 2 and alpha = .05) will be used. The two time-specific contrasts will be examined if the omnibus test is statistically significant to determine at which time points significant differences are present (each tested at alpha = .05). The two time-specific contrasts (to determine at which time points significant differences are present) will only be examined if the omnibus test is significant and, hence, the family-wise type I error rate of finding at least one significant difference at the three time points is controlled at alpha = .05. Hypotheses in relation to secondary outcomes of momentary self-esteem, positive and negative schematic beliefs of self, resilience, emotional well-being, general psychopathology, functioning, and quality of life at post-intervention and 6-month follow-up will be tested following the same steps. The investigators will access the trial data set to test hypotheses in relation to all four time points (i.e., post-intervention, 6-month, 18-month, and 24-month follow-up) in a priori planned statistical analysis when data collection for assessments at 24-month follow-up has been completed. For hypotheses in relation to primary and secondary outcomes at all four time points (i.e., post-intervention, 6-month, 18-month, and 24-month follow-up), the main effect of condition will be tested using, again, an omnibus test of no difference between the two groups at all four time points (Wald-type test with df = 4 and alpha = .05). The four time-specific contrasts will be examined to determine at which time points significant differences are present (each tested at alpha = .05), if the omnibus test shows to be statistically significant. Since randomization will be performed in blocks, stratified by region of collaborating center or as external admission, all analyses will include this as a covariate, even though it is not expected this variable will lead to bias. As participants will be randomly assigned to experimental and control condition, no differences across conditions are expected in other study parameters (socio-demographics, alcohol and substance use, medication use, treatment classification, social support and self-compassion). If, however, in contrast to what would be expected, there are significant differences at baseline in any of these parameters across conditions, these will be included as covariate(s) in analyses with primary and secondary outcomes as dependent variable. As ESM data have a multilevel structure, multiple ESM observations (level 1) will be treated as nested within time points (i.e., baseline, post-intervention and 6-month, 18-month, and 24-month follow-up) (level 2) and time points will be treated as nested within subjects (level 3).

Cost-effectiveness analysis (CEA) will be conducted based on service use and cost data collected using the TiC-P. Cost-utility analysis (CUA) will be conducted using quality-adjusted life years (QALYs), which will be calculated based on the EQ-5D-5L. For both CEA and CUA, the incremental cost-effectiveness ratio (ICER) will be calculated, which reflects the extra cost needed (or saved) per one unit increase in self-esteem or QALY gained, respectively.

Descriptive statistics will be used and confidence intervals constructed as appropriate to compute basic sample characteristics and summarize findings on acceptability, safety, and intervention fidelity of, as well as adherence to the intervention.

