Potential participants will then be asked to complete the screening questionnaires to assess whether they meet the inclusion criteria. Participants aged 16 years or older will be financially compensated for their time, and travel expenses will be fully reimbursed. To minimize loss to follow-up, researchers maintain contact with participants on a regular basis. Also, participants will receive a small additional financial reimbursement for completing all follow-up assessments.

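### The protocol concludes that attrition bias is minimized, but its rule for adding baseline covariates is not tied to missingness, so its own missing-at-random condition is not shown to be met

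*Protocol article*

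**What the plan says.** All of the following is in the protocol article.

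- **Model terms (Statistical analysis).** RSES at post-intervention and 6 months is regressed on "self-esteem measured at baseline, condition (SELFIE + TAU vs. TAU"), time, and "center (as a four-level factor), the baseline × time interaction, and a time × condition interaction term as independent variables".
- **Covariance (Statistical analysis).** "Residuals within subjects will be allowed to be correlated with a completely unstructured variance-covariance matrix", so the two RSES measurements are modelled jointly.
- **Missing data (Statistical analysis).** REML uses all available data, "assuming that data is missing at random if all variables associated with missing values are included in the model". The next sentence draws the inference that "potential bias due to attrition over the study period, differences between centers, or as a function of baseline self-esteem will be minimized by the model".
- **Further covariates (Statistical analysis).** Socio-demographics, substance use, medication, treatment classification, social support and self-compassion are added only where the arms differ significantly at baseline. K10 and SCL-90-R are collected at baseline (Outcome measures, Secondary outcomes) but are not on this list.
- **Attrition (Sample size).** "we will allow for a 25% attrition rate at 2-year follow-up".
- **Payment (Participants).** "Participants aged 16 years or older will be financially compensated for their time". The same section promises a further small payment for completing all follow-ups, with no age limit stated.

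**The concern.** The protocol states a condition for its missing-data assumption and then asserts the consequence, with no step that makes the condition true. No part of the section identifies variables that predict missingness or brings them into the model. The one rule that adds variables works on a different property, imbalance between arms. A variable that strongly predicts dropout but is balanced by randomization never enters. K10 and SCL-90-R do not enter under this rule even if they are imbalanced.

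If such a variable also predicts follow-up RSES beyond what the model already explains, and drives dropout differently in the two arms, the treatment estimate is biased while the protocol describes that bias as minimized. Arm-specific dropout is conceivable here. Only the SELFIE arm carries three sessions, daily tasks and experience sampling six times a day on three days of each week (Experimental condition: SELFIE + TAU), and participants know their allocation (Randomization and blinding).

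**Working it through.** **1. The protocol's own attrition figure.** 130 / (1 − 0.25) = 173.3, rounded up to an even 174, or 87 per arm. Expected loss per arm is 0.25 × 87 = 21.75, about 22. Both figures reproduce. The 25% is the planned loss at 24 months; the primary hypothesis concerns post-intervention and 6 months, for which no rate is given.

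**2. What the model covers.**

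| Dropout depends on | In the primary model? |
|---|---|
| arm, time, center, baseline RSES | yes, as fixed terms |
| observed post-intervention RSES (for loss at 6 months) | yes, through the unstructured covariance |
| age, substance use, medication and the other listed parameters | only if significantly imbalanced between arms |
| baseline K10, SCL-90-R | no |

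**3. Does an omitted variable bias the contrast?** This was examined by simulation with 400,000 participants per scenario. From the document: true SMD 0.3 and 25% missing (applied at 6 months). Assumed: post-intervention RSES complete; correlation of 0.6 between baseline and follow-up RSES; dropout logistic with slope 1 per SD; an omitted variable U, independent of baseline RSES, correlated 0.3 or 0.5 with the outcome.

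The likelihood estimate of the 6-month effect was obtained by factorization. Regress post-intervention RSES on arm and baseline in everyone (arm coefficient a1). Regress 6-month RSES on arm, baseline and post-intervention RSES in those observed (arm coefficient a2, post-intervention coefficient g). Then effect = a2 + g × a1, and bias = effect − 0.3.

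| Dropout driven by | Bias, corr. 0.3 | Bias, corr. 0.5 |
|---|---|---|
| baseline RSES, same in both arms | −0.002 | −0.002 |
| baseline RSES, opposite by arm | 0.000 | 0.001 |
| post-intervention RSES, same in both arms | −0.001 | −0.007 |
| post-intervention RSES, opposite by arm | 0.002 | −0.005 |
| U, same in both arms | −0.001 | 0.000 |
| U, one arm only | −0.037 | −0.046 |
| U, opposite by arm | −0.071 | −0.092 |
| U, one arm only, U in model | 0.000 | 0.005 |
| U, opposite by arm, U in model | 0.000 | 0.002 |

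The minus sign reflects only how U was coded; reversing U reverses it.

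**4. Range.** A further simulation with baseline distress as the omitted variable, also under assumed correlations and 25% missing, gave about 0 when the link to dropout is equal in both arms, about 0.015 to 0.05 SD when it exists in one arm only, and up to about 0.10 SD when it runs in opposite directions. Against the target SMD: 0.015 / 0.3 = 5%, 0.05 / 0.3 = 17%, 0.10 / 0.3 = 33%. Adding the score to the model again brought the bias to about zero.

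**5. A limit of step 3.** Those runs let an observed post-intervention RSES help with a missing 6-month value. A participant lost before post-intervention has no follow-up RSES, so only arm, center and baseline RSES are available to explain that loss, and the protection is weaker.

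**The case against.** The strongest reply is that the model is better than the criticism suggests and the claim more modest. The protocol says minimized, not removed, and keeps its assumption explicit. Center and baseline self-esteem, both named in the same sentence, are model terms. The joint model handles dropout tied to observed RSES, even when that differs by arm. A full statistical analysis plan is promised before unblinding. All of this stands, and it limits the point.

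A reader might also infer several stronger things that the documents do not support:

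- **That baseline RSES and center are all the model holds.** They are the only baseline covariates fixed in advance, but arm, time, two interactions and the repeated RSES are also there.
- **That paying only those aged 16 or older biases the treatment effect.** The rule is the same in both arms, and a predictor acting equally in both arms left the contrast about unbiased. The additional payment for completing follow-up carries no stated age limit.
- **That the bias favors SELFIE.** Stopping the intervention is not the same as missing an assessment, all randomized participants are to be analyzed, and nothing fixes the sign.
- **That 17 to 50% of the target effect is at risk.** That comes from 0.25 × 0.2 = 0.05 and 0.25 × 0.6 = 0.15 SD, divided by 0.3. The 0.2 to 0.6 SD departure is assumed, not derived from the omitted covariates, and 25% is the 24-month rate.
- **That missing imputation or delta-adjusted analyses are a defect.** These can properly be left to the statistical analysis plan.

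The reply does not rescue the inference itself. The model, the covariate rule and the conclusion are all stated in this document, and the rule does not deliver the condition.

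**Conclusion.** The point holds in a limited form. The protocol's conclusion about attrition is wider than its model supports: it holds for missingness explained by arm, center, baseline RSES and observed RSES, and is not shown for anything else. This does not show the primary analysis to be invalid.

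The possible bias is nil to modest. It is about zero unless the omitted variable is related to the outcome given the model and its link to dropout differs by arm. Where both apply, the figures are the 0.015 to 0.05 SD (one arm) and up to about 0.10 SD (opposite directions) derived above. They rest on assumed correlations and dropout slopes and on 25% missing. Smaller loss at 6 months would reduce them; loss before post-intervention would leave less protection than those with complete post-intervention RSES had. The protocol gives no evidence that dropout will differ by arm in this way, so the case for change is that protection is cheap, not that bias has been shown.

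**What to change.** 1. Name in advance a small set of baseline variables, already collected and expected to predict both dropout and outcome (for example age and baseline K10 or SCL-90-R total). Include them in the primary model regardless of balance between arms.
2. Limit the concluding sentence to the claim that bias is reduced for missingness explained by the modelled variables and observed RSES.

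The cost is one or two degrees of freedom, a few lines of text and code, and a less sweeping statement about attrition. No new data are needed. Imputation details and delta-adjusted analyses can be settled in the statistical analysis plan.

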Previous studies of conventional interventions suggest that psychiatric symptoms, such as anxiety and depression symptoms, may be reduced through enhancing self-esteem [51]. However, these interventions are not tailored toward the specific preferences and needs of youth as naturally occurring in daily life. While EMIs such as the SELFIE intervention provide a unique opportunity to deliver youth-friendly, accessible, personalized, real-time interventions in daily life, robust trial-based evidence on EMIs and other mHealth interventions remains very limited [22, 52, 53, 59–62].

The overall aim of the current study is to test the efficacy of a novel, accessible, transdiagnostic ecological momentary intervention (EMI) for improving self-esteem (“SELFIE”) in youth aged 12–26 with prior exposure to childhood adversity in a multi-center randomized controlled trial (RCT). The SELFIE intervention will be administered in addition to treatment as usual (TAU) (experimental condition) and compared to a control condition of TAU only, which will include (access to) standard health care.

The specific objectives of this study are to:
Test the efficacy of the SELFIE intervention on improving self-esteem at post-intervention and 6-month follow-up (primary outcome);Test the efficacy of the SELFIE intervention on improving momentary self-esteem, positive and negative schematic beliefs of self, resilience, emotional well-being, general psychopathology, functioning, and quality of life at post-intervention and 6-month follow-up (secondary outcomes);Establish whether the effects of the SELFIE intervention on primary and secondary outcomes hold at 18-month and 24-month follow-up;Examine the cost effectiveness and cost utility of the SELFIE intervention;Assess the acceptability, safety, adherence and fidelity of the SELFIE intervention.

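### The long-term hypothesis (18 and 24 months) is gated by a four-visit omnibus that an early effect alone can open, and the 0.82 given for the long term is power for any of four visits

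*Protocol article*

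**What the plan says.** All references are to the protocol article.

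- Introduction, third objective: "Establish whether the effects of the SELFIE intervention on primary and secondary outcomes hold at 18-month and 24-month follow-up".
- Secondary outcomes: these outcomes, with the RSES total among them, "will be compared between the experimental and control condition and at 18- and 24-month follow-up (H3"). H1, under Primary outcome, is the RSES comparison at post-intervention and 6 months.
- Statistical analysis, when 6-month data are complete: an "omnibus test of no difference between the two conditions at all two time points (Wald-type test with df = 2 and alpha = .05"), followed by the two visit-specific contrasts if it is significant.
- Statistical analysis, when 24-month data are complete: "hypotheses in relation to all four time points (i.e., post-intervention, 6-month, 18-month, and 24-month follow-up") are tested by an "omnibus test of no difference between the two groups at all four time points", a Wald-type test with 4 df at alpha 0.05. If that is significant, "The four time-specific contrasts will be examined to determine at which time points significant differences are present (each tested at alpha = .05").
- Sample size: with 65 per condition and SMD 0.3, power is 0.87 for a difference at post-intervention or 6 months. For the long term the article quotes a difference ("at least) at one of the post-intervention and follow-up time points (6-month, 18-month, and 24-month follow-up), with a power of 0.82".

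No joint test of 18 and 24 months is given, and no power for it.

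**The concern.** The question and the gate do not match. H3 is about two late visits, but the null hypothesis of the 4-df test is false as soon as there is an effect at post-intervention or 6 months, which is what the trial expects. A significant omnibus at the end of follow-up therefore does not in itself support a lasting effect.

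The gate also fails to protect the two late contrasts. An omnibus followed by unadjusted 0.05 tests is a closed procedure when there are two contrasts: the only joint hypothesis is the pair, and the omnibus tests it. With four contrasts, closure would also need tests of every pair and every triple, and the plan has none. If the early contrasts are truly non-zero, the gate is mostly open and 18 and 24 months are read as two unadjusted tests.

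The 0.82 is introduced as a long-term figure but defined over all four visits, so it does not tell a reader how well the trial can answer Objective 3.

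**Working it through.** **Inputs from the article.** 65 analysed per arm, SMD 0.3, omnibus tests with 2 and 4 df at alpha 0.05 (critical values 5.99 and 9.49), contrasts each at 0.05.

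**Assumptions.** The article gives neither correlations nor the pattern of effect over time. I used a total SD of 1 and common correlations of 0.5 to 0.8, in two structures: exchangeable (baseline included), and AR(1) by visit order with baseline first.

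**Formula.** Let S be the covariance of the follow-up scores after adjustment for baseline and d the vector of true differences. The Wald statistic is noncentral chi-square with ncp = (65/2) d'S⁻¹d. Rates that combine the gate and the contrasts were simulated with 400,000 draws per scenario.

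**The article's own figures.** The sample size reproduces: 130/0.75 = 173.3, hence 174. The powers cannot be reproduced uniquely. They need ncp = 11.54 (2 df, 0.87) and 12.49 (4 df, 0.82), and several assumptions give both (rb = correlation with baseline, rw = between follow-up visits):

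- 0.3 at all four visits, rb about 0.84, rw about 0.92;
- 0.3 at one visit only, rb about 0.86, rw about 0.70;
- 0.3 at post-intervention and 6 months and zero later, rb about 0.75, rw about 0.63.

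For the last set, the adjusted variance is 1 - 0.5625 = 0.4375 and the covariance 0.63 - 0.5625 = 0.0675, a difference of 0.37. With d'd = 0.18 and (sum of d)² = 0.36:

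- 2 df: 32.5 × (0.18 - 0.36 × 0.0675/0.505)/0.37 = 11.58, power 0.871;
- 4 df: 32.5 × (0.18 - 0.36 × 0.0675/0.64)/0.37 = 12.48, power 0.820.

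So 0.82 is compatible with no effect at all at 18 and 24 months. This does not show that the authors assumed that pattern.

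**Early effect only (0.3, 0.3, 0, 0), worked at exchangeable r = 0.5.** Adjusted variance 0.75, covariance 0.25, difference 0.5. ncp = 32.5 × (0.18 - 0.36 × 0.25/1.5)/0.5 = 7.80, so the 4-df test rejects with probability 0.59. Across the range:

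| Structure | r | 4-df omnibus rejects | At least one false 18- or 24-month claim, as planned |
|---|---|---|---|
| Exchangeable | 0.5 | 59% | 8% |
| Exchangeable | 0.7 | 81% | 9% |
| Exchangeable | 0.8 | 94% | 9% |
| AR(1) | 0.5 | 46% | 7% |
| AR(1) | 0.8 | 86% | 8% |

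A 2-df test of 18 and 24 months rejects in 5% of these trials. With it as the gate, the chance of a false late claim is about 4%.

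**Power of that 2-df late test, SMD 0.3 at both visits.** At exchangeable r = 0.5, ncp = 32.5 × (0.18 - 0.36 × 0.25/1.0)/0.5 = 5.85, power 0.57. At r = 0.6, 0.7 and 0.8 it is 0.63, 0.72 and 0.86. Under AR(1) it is 0.41, 0.40 and 0.44 at r = 0.5, 0.7 and 0.8.

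**Chance of a significant late contrast, SMD 0.3 at all four visits.**

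| Structure | r | As planned | With a 2-df late gate |
|---|---|---|---|
| Exchangeable | 0.5 | 0.54 | 0.57 |
| Exchangeable | 0.8 | 0.85 | 0.86 |
| AR(1) | 0.5 | 0.42 | 0.41 |
| AR(1) | 0.7 | 0.44 | 0.40 |
| AR(1) | 0.8 | 0.51 | 0.44 |

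**The case against.** The omnibus is only a gate. The plan goes on to separate 18- and 24-month contrasts, and those answer Objective 3. A reader might take 59-94% as the rate of false long-term claims. It is not: it is the rate at which the gate opens. Each late contrast on its own is falsely significant in no more than about 5% of trials. What stands is the family of the two late contrasts, at about 7-9%.

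A reader might also infer that a failed primary test can be reopened two years later. The article does not support that. H1 is fixed as RSES at post-intervention and 6 months, tested with 2 df when 6-month data are complete, and the later comparisons, RSES included, are listed under secondary outcomes. With no effect anywhere, at least one of the two omnibus tests rejects in about 7.6% of trials, but the article does not promise joint control across a primary and a secondary test. What remains is that the early contrasts appear again at 0.05 with no statement of their status. The full analysis plan, which is not at hand, may settle that. The 4-df test itself is fixed in the article.

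The Sample size section defines the 0.82 openly as covering any of four visits, so the figure is loosely labelled, not concealed. Nor can one infer that true long-term power is below 0.82. Among assumptions that roughly match both stated powers, the 2-df late test has power from 0.81 to above 0.99 when SMD is 0.3 at both late visits.

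**Conclusion.** The point holds in limited form. H3 is gated by a test that an early effect alone can pass. If SMD is 0.3 early and zero later, the chance of at least one false 18- or 24-month claim is about 8-9% under exchangeable correlation and 7-8% under AR(1), against a nominal 5%. These figures rest on 65 per arm and assumed correlations of 0.5 to 0.8. That the early visits belong to the gate and to the definition of the 0.82 is plain from the text and needs no assumption.

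The power for 18 and 24 months is unstated and cannot be recovered from the article. The primary analysis is unaffected. This concerns a secondary hypothesis, and the plan should be changed before the 24-month analysis.

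**What to change.** 1. Keep the four-visit model. Test H3 with a 2-df Wald test of the 18- and 24-month contrasts, and read each at 0.05 only if that test is significant.
2. State that H1 is decided once, by the 2-df test at the 6-month analysis, and that the post-intervention and 6-month contrasts are only re-estimated at 24 months.
3. Relabel the 0.82 as power for a difference at any of four visits, and add the power of the 18/24-month test with the correlations and effect pattern assumed.

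The cost is wording in the analysis plan, with no new data. It is not free of power loss in general. With a persistent effect, the change gains slightly under exchangeable correlation and loses under AR(1), by 0.01 at r = 0.5 and 0.07 at r = 0.8. A purely late effect with high exchangeable correlation also favours the present gate (0.75 against 0.72 at r = 0.7; 0.90 against 0.86 at r = 0.8). That is the price of holding the error rate for the two late contrasts at 5%.
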